[figure not shown]

#### A3a. Financial Conflict of Interest

Does the investigator have a financial interest in any non-Baylor sponsor or funding source for this research?  
No

#### A5. Funding Source:

Organization: SEATTLE CHILDREN'S HOSPITAL RESEARCH FOUNDATION

#### A6a. Institutions where work will be performed:

Seattle Children's Hospital - Washington  
TCH: Texas Children's Hospital

#### A6b. Research will be conducted outside of the United States:

Country:  
Facility/Institution:  
Contact/Investigator:  
Phone Number:

If documentation of assurances has not been sent to the Office of Research, please explain:

#### A7. Research Category:

## Section B: Exempt Request

### B. Exempt From IRB Review

Not Applicable

## Section C: Background

Babies born prematurely the infant is at high risk for mortality and morbidity. Advances in acute supportive care have improved survival in infants less than 1500 grams, but these improvement in survival rates have plateaued over the last decade. Survival to discharge in this patient population is no longer the dominant goal in research efforts, which are now directed more toward decreasing the rates of complications in this vulnerable patient group. One of the most common complications of prematurity is the development of chronic lung disease, termed bronchopulmonary dysplasia (BPD). The exact pathophysiology of BPD has not been elucidated entirely, but the dominant pathophysiology is probably related to supportive care employed for infants with underdeveloped lungs, which can create lung injury and arrest alveolar development. Respiratory support for very low birth weight (VLBW) (< 1500 grams) infants has historically included mechanical ventilation, continuous positive airway pressure (CPAP) or no positive pressure, +/- supplemental oxygen. Mechanical ventilation damages the lung as it is non-physiologic, and no positive pressure is untenable because the respiratory system is immature to the extent that lung collapse ensues even when the lung mechanics are normal. CPAP assists spontaneously breathing infants by preventing lung collapse, and nasal CPAP, provided through nasal prongs, affords the additional benefit of avoiding the damaging effects of endotracheal intubation. Establishing the system pressure by having the system gas exit through a tube submerged in water, in addition to being much cheaper and easier to regulate than with a mechanical ventilator, provides additional benefits through the small pressure oscillations caused by the effects of the bubbling of the gas leaving the tube immersed in the water bath. Thus, providing respiratory support by bubble nasal CPAP (Bn-CPAP) in infants born at less than 30-32 weeks gestational age is being used by a growing number of NICUs in the US and around the world. Unfortunately, there is a significant failure rate for nasal CPAP, failure being the need for intubation for respiratory failure or significant apnea. Thus, there is a need for innovative new approaches for non-invasive respiratory support in premature infants to reduce complications of prematurity such as BPD. In addition, the great majority of the almost one million neonates who die each year due to respiratory insufficiency arising from their premature birth occur in low and middle-income countries (LMIC) and other resource-limited health care settings, in which intubation and mechanical ventilation are not available.

Colleagues from Seattle Children's Hospital have designed and developed a simple and inexpensive respiratory support device (Seattle-PAP) that is safe and effective in preclinical trials. The design is such that instead of the expiratory limb of the Bn-CPAP going straight into a column of water (0 degree angle), the expiratory limb is at the same depth so that the airway pressure is identical (to that set with Bn-CPAP) but gas flow exits through a tube bent to 135 degrees, up toward the surface of the water. In a model in vitro, this modification increases airway pressures oscillations in a model lung relative to standard Bn-CPAP. Seattle-PAP has been studied in experimental animals and found to provide superior support for the respiratory system. The endpoints assessed physiologically include:

1. Partial pressure of O2 in arterial blood (PaO2) with Seattle-PAP being higher than standard Bn-CPAP.
2. No differences in PaCO2 between groups.
3. Markedly lower work of breathing as assessed by a Pressure Rate Product.

Based on this study we propose to test the hypothesis that respiratory support with Seattle-PAP exhibits lower estimates of work of breathing in VLBW infants than standard Bn-CPAP.

No long term beneficial effect is expected to be observed in the infants to be studied in the trials proposed. Seattle-PAP may provide greater support than Bn-CPAP, and the physiological data assessed are designed to test the hypothesis of enhanced respiratory support, but we have made no provisions to continue the experimental device in the present trial, as Bn-CPAP is presently the Texas Children's Hospital (TCH) nursery standard for clinical care.

The data to be obtained in the studies proposed are essential to demonstrating device performance in humans, and may impact the following efficacy trial. The longer term goals of the studies planned are to improve non-invasive respiratory support, limit acute lung injury, and diminish chronic respiratory morbidity in a population highly susceptible to these complications of prematurity. The studies proposed are logical in sequence, and the results to be obtained are essential to determine whether Seattle-PAP has the potential to reduce the incidence of BPD and/or chronic respiratory morbidity in highly resourced NICUs and to prevent perhaps hundreds of thousands of neonatal deaths due to respiratory distress each year in resource-limited settings.

## Section D: Purpose and Objectives

We propose to test the hypothesis that Seattle bubble nasal continuous positive airway pressure (Seattle-PAP) supports respiratory physiology in very low birth weight (VLBW) infants more effectively than standard bubble nasal continuous positive airway pressure

(Bn-CPAP).

The primary outcome variable is work of breathing (WOB) over a two hour period, estimated from pressure-rate products, which are assessed with 6 Fr (2 mm) catheters placed in the distal esophagus for monitoring esophageal pressures (Pes), thereby estimating changes in pleural pressures during breath cycles. The following endpoints would also be assessed: Oxygen saturations and Fraction of Inspired Oxygen (FiO2) needed to keep saturations in acceptable ranges, Heart Rates (HR), transcutaneous carbon dioxide (TcPCO2), and respiratory rates throughout the 6 hour study period. The primary outcome measure will be evaluated during the last 15 minutes of each 2 hour study period. If the subject needs clinical interventions during this period, the closest preceding 15 minutes will be used for analysis.

Objective determination of when an infant requires more or less respiratory support is difficult, but measurements of pressure-rate products as estimates of work of breathing, using esophageal catheters, can estimate an infant's respiratory effort. However, objective, simple-to-use, low cost, and non-invasive methods and tools to determine an infant's respiratory effort do not exist currently.

This study also is designed to test the hypothesis that infants' chest and abdominal movements can be assessed quantitatively from video images in ways that can be correlated with intrathoracic pressures, as measured with esophageal catheters. The video procedures will be implemented when and if the process can be set up before the enrollment is completed.

## **Section E: Protocol Risks/Subjects**

### **E1. Risk Category**

Category 2: Research involving greater than minimal risk, but presenting the prospect of direct benefit to the individual subjects.

### **E2. Subjects**

Gender:

Both

Age:

Premature Infant (<37 weeks gestational age)

Ethnicity:

All Ethnicities

Primary Language:

English, Spanish

Groups to be recruited will include:

Patients

Vulnerable populations to be recruited as subjects:

Children

Vulnerable populations require special protections. How will you obtain informed consent, protect subject confidentiality, and prevent undue coercion?

Informed consent will be obtained from one or both parents of an eligible infant. Data will be entered prospectively during the study period, while demographics will be abstracted from the chart. All data will be recorded and coded. This will be explained to parents and they will have the right to withdraw from the study at any time.

### **E3. Pregnant woman/fetus**

Will pregnant women be enrolled in the research?

No

### **E4. Neonates**

Will neonates be enrolled in the research?

No

### **E5. Children**

Will children be enrolled in the research?

Yes

## Section F: Design/Procedure

### F1. Design

Select one category that most adequately describes your research:

i) Device, Phase I, Single Center

Discuss the research design including but not limited to such issues as: probability of group assignment, potential for subject to be randomized to placebo group, use of control subjects, etc.

This is a single site enrollment study with an enrollment target of 40 subjects. Texas Children's Hospital/Baylor College of Medicine will serve as the primary enrollment site.

Seattle Children's Hospital will provide Seattle-PAP and the comparator F&P BC 153-10 Bn-CPAP System (60 of each device). Seattle-PAP is provided under a 510(k) exemption; however, data may need to be submitted to US or international regulatory bodies in the future.

This is a pilot study in which each infant will serve as their own control. Study procedures will commence after informed consent is obtained and eligibility is confirmed. The study consists of 3 periods: (1) Bn-CPAP (~120 minutes) (2) Seattle-CPAP (~120 minutes) (3) Bn-CPAP (~ 120 minutes).

The subject's participation ends at the end of the 6 hour period. However, the study team will follow the subjects for targeted adverse events for 28 days from end of study AND 36 weeks gestational age OR discharge (whichever occurs first).

Inclusion Criteria:

1. Admitted to a bed at Pavilion for Women (or beds monitored by SickBay)
2. Less than or equal to 32 weeks gestational age
3. 6 to 72 hours of life (this parameter is chosen because this will be the time frame of subsequent non-inferiority trial).
4. Stable on standard bubble nasal CPAP (Bn-CPAP) defined as having less than 6 apneic spells per shift and requiring only tactile stimulation for treatment
5. On less than equal to 8 cm H2O on Bn-CPAP
6. Less than or equal to 30% oxygen requirement (this is chosen because if it is greater than 30% the patient is likely to have evolving hyaline membrane disease which is likely to dominate the serial measurements made and the effects of the device will be difficult to detect).
7. Informed Consent

Exclusion Criteria:

1. Congenital anomalies or suspected chromosomal abnormalities

### F2. Procedure

The study measurements will be recorded continuously over each of the three periods (outlined in section F1) of 2 hours for a total of 6 hours. If reasonable clinically, routine nursing care should be conducted in the first 15 min of each period of 2 h; however, patient care as per normal is the prime directive.

Study-Specific Monitoring Equipment:

Upon verification of subject eligibility the DAte ReCording Instrument (DARCI 1, DARCI 2), the Video Recording System, and TcPCo2 monitor will be set up.

To address the growing demand for continuous data recording during clinical trials, SCRI and Intellectual Ventures Labs (IV Lab) have created a rugged data recording instrument (DARCI) that will be used to monitor and record, and, with further development, transmit airway pressure (PAW) data continuously. In order to complete this data collection, DARCI will record the pressure present

at the junction between the breathing circuit and the nasal prongs. DARCI is designed to be easy to use by a trained study coordinator and operates in three different modes – Enrollment (the act of setting up the device for a new test), Recording (the act of collecting data from the Device Under Test [DUT]), and Download (the act of transmitting and storing the data collected onto a PC). The esophageal catheters are commercially available and will be supplied by the Sponsor. The catheter will transmit pressures to DARCI which will transmit the transpulmonary pressure data to Sickbay for the study duration.

The Video Recording System will be installed and activated when available. When the video recording has occurred, the DVR data will be downloaded to a hard disk and delivered to [name] for storage. Videos of the infants will be de-identified through the use of a standard phototherapy mask.

The additional monitoring equipment, a TcPCO2 monitor, will be set up and connected to the infant. The management of the oxygen administration and monitoring is per subjects' standard of care.

The physiological data described below will be captured in [name] database (SickBay) automatically as per H-28829 for the 6 hour study period.

• Heart rate • Respiratory rate • Blood pressure • SPO2 via Pulse oximetry. TCH patients are managed to keep the pulse oximetry between 90 and 95%. This range is evidence-based and is usually attained by respiratory support consisting of a combination of nasal CPAP (range 5-8 cm H2O) and FiO2. If the infant is on Bn-CPAP, then we would not expect an improvement, so the device should have no effect on percent saturation. The infant will still qualify for enrollment, as the other endpoints (TcPCO2 and pressure rate products) may indicate a difference of the new device, and the data will address whether Seattle-PAP leads to a deterioration. • TcPCO2, via transcutaneous PCO2 monitors. • ECG • Chest impedance pneumography • Airway and esophageal pressures via DARCI 1 and 2, respectively

The data points described below will also be captured in for the 6 hour study period:

• Demographics • Concomitant medication • Serious and non-serious adverse events • Start and Stop times of Bn-CPAP and Seattle PAP • FiO2, tube depth, gas flow rate

Study Start Time (T=0):

Once SickBay is capturing data from all the monitoring equipment, the PI/Co-I/respiratory therapist will place the esophageal catheter. Once the esophageal catheter is placed the CRA will verify that SickBay is capturing data transmitted by DARCI 2. Data collection for this study starts (T=0) once all the systems used to monitor the patient and airway and esophageal pressures are verified and working as required.

#### STUDY TIMEPOINTS:

See schedule of events attached in Section S.

##### I. Fisher-Paykel Bn-CPAP (0-2 Hours):

At T=0 (+ 5 minutes) the Respiratory Therapist will switch the patient from TCH's standard form of Bn-CPAP to the commercial Bn-CPAP Fisher-Paykel device (F&P Bn-CPAP).

##### II. Seattle-PAP (2-4 Hours):

At 120 minutes (+ 5 minutes), the Respiratory Therapist will switch the patient from F&P Bn-CPAP to Seattle-PAP for the following 2 hours (study period hours 2 to 4).

##### III. F&P Bn-CPAP (4-6 Hours):

At 240 minutes (+ 5 minutes) the Respiratory Therapist will switch the patient back to F&P Bn-CPAP.

##### IV. End of Study:

At 360 minutes (+ 5 minutes) the Respiratory Therapist will switch the patient back to TCH Bn-CPAP from F&P Bn-CPAP

##### V. Follow Up:

Follow up AE/SAE (Adverse Event/Serious Adverse Event) data collection will be performed at 28 days after enrollment, and at 36 weeks gestational age or discharge whichever is earliest.

Rationale for the study time points is as follows:

In this study, the infants will be observed continuously and closely for the entire time the infants are being assessed for the work of breathing. Unexpected observations will be reported and evaluated by the DSMB, sponsor, and IRB, as applicable. This is highly unlikely, as the preclinical studies indicated stability over a similar time frame. The 2 hour interval for study of Seattle-PAP was chosen, as this should allow ample time for us to assess the work of breathing on the device that reflects recruitment of the lung and differences in levels of respiratory support. The two hour periods were chosen as periods of time in which the infant will transition physiologically between the lung volume on standard Bn-CPAP and Seattle-PAP.

As stated earlier, a respiratory therapist that is an expert in all aspects of Bn-CPAP will be present throughout the 6 hour period, because we do not want the measurements of study parameters to be affected by changes arising from differences in patient management, such as with positioning of the nasal prong interfaces.

## Section G: Sample Size/Data Analysis

### G1. Sample Size

How many subjects (or specimens, or charts) will be used in this study?

Local: 40      Worldwide: 40

Please indicate why you chose the sample size proposed:

This will be a pilot study, and we have done a power analysis for differences in our study based on the preclinical studies done on rabbits in which studies with lavaged, sedated juvenile rabbits weighing around 1000 g were assessed for work of breathing, estimated as pressure x rate products (PRPs) comparing standard bubble nasal Bn-CPAP with Seattle-PAP, the difference in the means for PRPs in the n=12 rabbits studied was 148.24 cmH2O/min. The standard deviation of the differences, in the paired comparisons of Bn-CPAP vs. 135 degree Seattle-PAP, was 154.23. Sample size calculations for two-tailed alpha 0.05 gave n=11 and 14 for powers of 0.80 and 0.90, respectively. To allow for anticipated greater heterogeneity of the human infant population that we need to characterize, we propose to study 40 infants, with ongoing review of accumulating data by a qualified person not otherwise involved in the study.

### G2. Data Analysis

Provide a description of your plan for data analysis. State the types of comparisons you plan (e.g. comparison of means, comparison of proportions, regressions, analysis of variance). Which is the PRIMARY comparison/analysis? How will the analyses proposed relate to the primary purposes of your study?

The PRIMARY comparison will be work of breathing, as estimated by pressure-rate products, assessed in each patient in each of the three periods, the first being on standard Bn-CPAP, using the Fisher-Paykel bubble CPAP device. The second study period will be with Seattle-PAP, and the third period will be with return of the patient to FP-Bn-CPAP for characterization.

The primary outcome variable is work of breathing (WOB) over a two hour period, estimated from pressure-rate products, which are assessed with 6 Fr (2 mm) catheters placed in the distal esophagus for monitoring esophageal pressures (Pes), thereby estimating changes in pleural pressures during breath cycles. The following endpoints would also be assessed: Oxygen saturations and Fraction of Inspired Oxygen (FiO2) needed to keep saturations in acceptable ranges, Heart Rates (HR), transcutaneous carbon dioxide (TcPCO2), and respiratory rates throughout the 6 hour study period. The primary outcome measure will be evaluated during the last 15 minutes of each 2 hour study period. If the subject needs clinical interventions during this period, the closest preceding 15 minutes will be used for analysis.

The pressure-rate product (PRP) data will be assessed statistically by paired t-tests, with Bonferroni corrections for multiple comparisons. Lacking any relevant human data, we estimate sample size requirements from our preclinical data, obtained in studies with juvenile rabbits. These rabbits were of one sex, relatively homogeneous genetic background, and were not born prematurely, but data estimates of differences in means and SDs of differences, with a power of 0.9, indicates 17 subjects are needed, with alpha 0.05.

Also, the study plans are to use video recording of the infants' breathing motions to test the hypothesis that methods of assessments of those recorded breathing motions can be correlated with measured PRPs to identify a method of producing objective assessments of work of breathing from video clips.

The assessments of PRPs in infants on Seattle-PAP have not been conducted previously, so we may encounter some learning curve issues, and even more likely to impact needs for additional study subjects is the even more distal efforts to characterize Work of Breathing (WOB) by analyses of video recordings. Consequently, we propose to study 40 infants.

Standard adverse events in this patient population include mortality and complications of prematurity, which include bronchopulmonary dysplasia (BPD), intraventricular hemorrhage (IVH), retinopathy of prematurity and necrotizing enterocolitis (NEC). The inclusion criteria being stable and on nasal CPAP will minimize the possibility that these complications would happen, but some infants will experience these adverse events as complications of prematurity.

Two hours of a different form of nasal CPAP is considered to be unlikely to be related to an increase in any of these adverse events. However, we will track and report these adverse events and they will be evaluated by [name] and/or Drs. [name] and [name]. These adverse events rarely are evident in the first 3 days of a stable patient, but they will be tracked and assessed by the investigators for 28 days after the study intervention day, and 36 weeks gestational age or discharge (whichever is earlier). At a biweekly meeting of investigators, including study respiratory therapists, the patients' data will be evaluated and adverse events discussed. If in this patient population, adverse events are accumulate at a rate greater than the general population of similar patients, we would stop the study and review possible mechanisms.

Furthermore, adverse events will be reviewed according to the BCM procedures regarding potential unanticipated problems involving risks to subjects.

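### The rule that replaces the primary-outcome window after any clinical intervention can drop respiratory worsening from the device comparison, and the outcome's time span is worded in two ways

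*Protocol*

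**What the plan says.** Sections D and G2 of the protocol carry the same three statements. The first names the outcome: "The primary outcome variable is work of breathing (WOB) over a two hour period, estimated from pressure-rate products". The second says when it is scored: "The primary outcome measure will be evaluated during the last 15 minutes of each 2 hour study period". The third is the fallback: "If the subject needs clinical interventions during this period, the closest preceding 15 minutes will be used for analysis".

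Neither section says what counts as a clinical intervention, whether *this period* is the 15-minute window or the two-hour period, or whether the replacement must come from the same device.

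Three other places bear on this:

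- **Switch times (Section F2, time points I to III).** The first period starts on F&P Bn-CPAP. Then "At 120 minutes (+ 5 minutes), the Respiratory Therapist will switch the patient from F&P Bn-CPAP to Seattle-PAP for the following 2 hours", and "At 240 minutes (+ 5 minutes) the Respiratory Therapist will switch the patient back to F&P Bn-CPAP".
- **Nursing care (Section F2).** Where clinically reasonable, "routine nursing care should be conducted in the first 15 min of each period of 2 h", but normal patient care takes priority.
- **Rationale for the timing (under V. Follow Up).** Each two-hour period is described as a time of physiological change, in which lung volume moves from its level on one device to its level on the other.

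**The concern.** A two-hour average and a last-15-minute value are different quantities while the infant is still moving from one state to the other, and the protocol expects that movement within each period. The two-hour span also takes in the time set aside for nursing care.

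The fallback is the more serious matter. The need for intervention arises after the switch, and the device may influence it: Section C describes failure of nasal CPAP as intubation for respiratory failure or significant apnoea. A rule that replaces data because of such an event lets the outcome help choose the data analysed. Routine handling, which is a good reason to move a window, is treated like intervention for worsening breathing, which is part of what the study wants to measure. If one device leads to more late worsening, discarding those segments favours that device.

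**Working it through.** **Inputs from the protocol.** Mean paired PRP difference in rabbits 148.24 and SD of the paired differences 154.23 (Section G1); 120-minute periods with a +5 minute switch window (Section F2); scoring window at minutes 105 to 120 of each period (Sections D and G2).

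**The plan's own figure.** d = 148.24 / 154.23 = 0.961. The exact paired t-test at two-tailed alpha 0.05 gives n = 11 (power 0.819) and n = 14 (power 0.913), which reproduces the 11 and 14 in Section G1. The SD of 154.23 is therefore used below as the scale of the paired difference.

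**1. Two-hour mean against the last 15 minutes.** Assume that PRP approaches its new level exponentially after the switch, with time constant τ. The protocol gives no τ. The share of the full effect seen between minutes a and b is

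1 − [τ/(b − a)] × [exp(−a/τ) − exp(−b/τ)].

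| τ (min) | Mean over 0–120 | Mean over 105–120 | Ratio | Less effect |
|---|---|---|---|---|
| 20 | 0.834 | 0.996 | 0.837 | 16% |
| 30 | 0.755 | 0.976 | 0.773 | 23% |
| 60 | 0.568 | 0.846 | 0.671 | 33% |

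The comparison has to be with the last-15-minute value, because that value is itself short of the full effect when τ is long.

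**2. Where the fallback window lies.** Suppose the intervention starts between minutes 105 and 120 of the period. Fifteen minutes ending at its start then begin at minute 90 to 105. Moving the whole window back gives minutes 90 to 105. Both lie on the same device.

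Now suppose *this period* means the two-hour period and the intervention starts t minutes after the actual switch. The minutes on the previous device are max(0, 15 − t): 15, 10, 5 and 0 for t = 0, 5, 10 and 15. With the +5 minute switch window, this can affect interventions that start up to 20 minutes into the nominal period.

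**3. Size of the shift if worsening is removed.** Let a fraction q of infants worsen by D SD of the paired difference on one device only, and let the fallback remove all of it. The shift in the mean difference is q × D. Both q and D are assumptions.

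| q | D | Shift (SD) | Shift in PRP (× 154.23) | Share of 148.24 |
|---|---|---|---|---|
| 5% | 1 | 0.05 | 7.7 | 5% |
| 10% | 1 | 0.10 | 15.4 | 10% |
| 10% | 2 | 0.20 | 30.8 | 21% |
| 20% | 2 | 0.40 | 61.7 | 42% |

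Each row is an upper bound for its scenario. A window that ends at the intervention would keep some of the lead-up.

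**The case against.** **Two time spans.** It is tempting to infer two rival primary analyses. The protocol does not support that. The later, specific sentence says how the outcome is scored, placing nursing care early keeps the end of each period clean, and no section plans a two-hour mean. This half is a wording repair.

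**The other device.** A reader might infer that the fallback will often borrow data from the other device. That needs *this period* to mean the full two hours and an intervention within 15 minutes of the switch. If routine care counted as an intervention, the care planned for the start of each period would then trigger the fallback by design and defeat the last-15-minute rule. Section G2 also says the outcome is assessed in each of the three periods. What stands is that no sentence excludes a crossing.

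**Lost worsening.** The 15 minutes ending at the intervention is one natural reading of the rule, and it keeps the lead-up. Data recorded during or after hands-on care also reflect that care, so setting them aside is defensible. The infants are selected to be stable: at most 30% oxygen, and fewer than six apnoeic spells per shift needing only tactile stimulation. These points limit the size. They do not remove the problem, because the text also allows the whole window to be moved back and does not define the trigger. It is not even clear whether tactile stimulation counts.

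**Who picks the window.** Because the sequence is fixed, a reader might infer that the person choosing windows knows the device. The protocol does not say who chooses or whether recordings are coded. Such detail is commonly left to the statistical analysis plan, which is not at hand.

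**Conclusion.** The point holds in a limited form. The protocol itself states a fallback rule that treats routine care and intervention for respiratory worsening alike. On one open reading, the rule can remove worsening from the comparison and favour the device on which more infants worsen. The shift is at most 0.05 to 0.40 SD of the paired difference, assuming that 5% to 20% of infants worsen by 1 to 2 SD on one device only and that all of it is removed. Nothing in the protocol fixes those values, and the stable population makes the lower end more plausible.

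The two-hour phrase should go, because a two-hour mean would understate the effect by about 16% to 33% relative to the operative window, for assumed time constants of 20 to 60 minutes. A figure as high as 43% (1 − 0.568 at τ = 60) might be inferred, but it compares the two-hour mean with the full steady-state effect and not with the last 15 minutes. Use of the other device's data is a gap in the rule and not its ordinary result.

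The change should be made. It concerns the primary outcome and needs no new data.

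**What to change.** In Sections D and G2:

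1. Delete the two-hour phrase and define the primary outcome as PRP in the last 15 minutes of each period.
2. State that *this period* in the fallback sentence is that 15-minute window.
3. Define the fallback as the 15 minutes ending at the start of the intervention, within the same period and on the same device, and no earlier than a fixed minimum time after the switch, which the investigators should set in advance.
4. Say which interventions trigger the fallback, and separate routine care from intervention for respiratory worsening.
5. Report the number of replaced windows and the reasons, by device.
6. Add a sensitivity analysis that uses the original window in every infant.

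The cost is a few sentences and slightly more analysis, since Section F2 already records continuously for six hours. The downside is that a few noisier values enter the comparison. These are analysis rules and leave clinical care unchanged. Coded window selection and a formal failure endpoint would be optional additions; their absence is not an error.

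### G2's Bonferroni-corrected paired t-tests on a fixed Bn-CPAP, Seattle-PAP, Bn-CPAP order are open to drift; one bracketing contrast would be a cheap improvement

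*Protocol*

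**What the plan says.** Protocol F1 gives one order for all infants: "The study consists of 3 periods: (1) Bn-CPAP (~120 minutes) (2) Seattle-CPAP (~120 minutes) (3) Bn-CPAP (~ 120 minutes". There is no randomised order and no concurrent control: "This is a pilot study in which each infant will serve as their own control".

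Protocol G2 answers the form's question about the primary comparison with "The PRIMARY comparison will be work of breathing, as estimated by pressure-rate products, assessed in each patient in each of the three periods". The method is "The pressure-rate product (PRP) data will be assessed statistically by paired t-tests, with Bonferroni corrections for multiple comparisons". On the last period, G2 says only that "the third period will be with return of the patient to FP-Bn-CPAP for characterization". The reading window is fixed: "The primary outcome measure will be evaluated during the last 15 minutes of each 2 hour study period".

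The pairs, their number and the rule for success are not given. Nor is any averaging of the two Bn-CPAP periods, or any term for time.

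On sample size, G1 states "Sample size calculations for two-tailed alpha 0.05 gave n=11 and 14 for powers of 0.80 and 0.90, respectively". G2, from the same rabbit data, states 17 infants for power 0.9 at alpha 0.05.

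**The concern.** With a fixed order, Seattle-PAP against period 1 is the device effect plus two hours of change in the infant. Seattle-PAP against period 3 is the device effect minus the next two hours of change. Under a steady trend the two tests err in opposite directions and can disagree. If either may carry the claim, a trend alone can produce it. If both must succeed, Bonferroni is not needed, and a trend hides a real effect in one of them.

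Some change over time is plausible on the protocol's own account. The infants are 6 to 72 hours old. The 30% oxygen limit in F1 was chosen because evolving lung disease could dominate serial measurements. The stability cited in the rationale for the study time points is preclinical. At stake is how the study's main result is read, and Section I makes later trials depend on that result.

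**Working it through.** **1. Inputs.** From G1: rabbit mean paired difference 148.24 and SD of differences 154.23, so d = 148.24 / 154.23 = 0.961. Planned n = 40. Assumptions not in the documents: drift per period in units of the SD of one paired difference; equal variances and equal correlations between periods; normal errors.

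**2. The protocol's own sample sizes** (exact noncentral-t paired test, two-sided):

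| Alpha | n for 80% | n for 90% |
|---|---|---|
| 0.05 | 11 | 14 |
| 0.05/2 = 0.025 | 13 | 17 |
| 0.05/3 = 0.0167 | 15 | 18 |

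G1's 11 and 14 are reproduced at 0.05. G2's 17 is not a single test at 0.05 (that gives 14) and not three tests (18). It matches 0.025, that is, two Bonferroni-corrected tests. G2 does not say that its alpha was divided.

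**3. Effect of a linear trend.** Let θ be the device effect on PRP (negative favours Seattle-PAP) and τ the change per period. The period means are μ, μ + τ + θ and μ + 2τ. Then:
- period 2 − period 1 = θ + τ
- period 2 − period 3 = θ − τ
- period 2 − mean(period 1, period 3) = θ

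**4. False wins, n = 40, θ = 0.** Two tests at 0.025 each, PRP falling by τ per period. The Seattle-PAP versus period 1 statistic is noncentral t with 39 df and noncentrality τ√40, with critical value 2.33. For drift of 0.1 SD or more, the period 3 test adds almost nothing.

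| Drift per period (SD) | At least one test favours Seattle-PAP | Single contrast at 0.05 |
|---|---|---|
| 0 | 2.4% | 2.5% |
| 0.1 | 5.2% | 2.5% |
| 0.2 | 15.5% | 2.5% |
| 0.3 | 34% | 2.5% |
| 0.5 | 79% | 2.5% |

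A rising trend gives the same rates through period 3.

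**5. If both tests must win.** False wins under linear drift are about 0%. Power suffers: for a true effect of 0.4 SD with 0.3 SD drift it is about 5%, against 81% for the contrast. For half the rabbit effect (74 / 154.23 = 0.48 SD) with 0.5 SD drift it is about 1%, against 93%.

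**6. Precision.** With within-infant variance σ² per period, one pair has variance 2σ². The contrast has σ²(1 + 1/4 + 1/4) = 1.5σ². The SD ratio is √(1.5/2) = 0.866, so 13% smaller (133.6 against 154.23). At half the rabbit effect, n = 40 and no drift, power is 76% for one named pair at 0.025, 89% for either of two and 93% for the contrast. At the full rabbit effect all exceed 99.9%.

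**7. Where the contrast fails.** With a one-off step s between periods 1 and 2 and nothing after, the contrast is biased by s/2. In units of its own SD that is (s/2)/0.866. For s = 0.3 and 0.5 SD, its false-win rate is 19% and 43%, against about 34% and 79% for the two planned tests.

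**The case against.** The strongest reply is that the pairs, their number and the success rule are commonly left to an analysis plan, and none is shown here. Paired t-tests with Bonferroni are valid for pairwise questions. This stands as far as the omissions go. What remains is that G2 names this method as primary, and the method does not use the two Bn-CPAP periods together.

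A reader might infer that the protocol lets either test win. It does not say so. The match of 17 to alpha 0.025, and the fact that Bonferroni is needed only when one success is enough, support that reading but do not establish it.

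A reader might also infer that period 3 was put there to remove drift and that this protection is thrown away. The document gives its purpose only as characterization. The pairwise set can also reveal a trend. With all three pairs tested at 0.0167 and 0.3 SD drift, Seattle-PAP falsely wins against period 1 in 29% of trials, and period 1 versus period 3 is significant in 98% of those. No written rule acts on that signal, however.

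The drift sizes are assumptions, and the protocol limits drift: stable infants on at most 30% oxygen, nursing care early in each period where reasonable, a respiratory therapist present throughout, and readings in the last 15 minutes. The catheter is in place before T=0, and a device swap opens every period, so neither singles out period 1 strongly. At 0.1 SD the excess is small.

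Finally, a loss of power is no argument at the design effect, where 40 infants give over 99.9% even with Bonferroni.

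**Conclusion.** The point holds as an advisable improvement. The stated primary method is exposed to a linear time trend that a single contrast would cancel. Under the best-supported reading (two tests at 0.025, either may win), the favourable false-win rate runs from about 5% to 79% for drift of 0.1 to 0.5 SD per period. With no drift it is 2.4%, and there is no problem. Under a both-must-win reading the cost is power instead.

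These figures rest on n = 40, linear drift of assumed size, and equal variances and correlations between periods. The precision gain matters only for effects well below the rabbit effect.

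It would go too far to call the trial's error rate inflated by a known amount, since neither the drift nor the success rule is documented. It would also go too far to say that the contrast cures the fixed order: a settling step after period 1 still gives 19% to 43% false wins. For a pilot, this is not a must-fix error.

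**What to change.** In G2, replace the sentence on paired t-tests with one primary contrast per infant: PRP on Seattle-PAP minus the mean of that infant's two Bn-CPAP periods. Test it by a paired t-test at two-sided 0.05, report a 95% confidence interval, and apply no Bonferroni correction to it. Report Seattle-PAP versus period 1, Seattle-PAP versus period 3, and period 3 versus period 1 as supportive estimates, the last as a check for drift or carry-over. State the alpha behind the sample size figure in G2 so that it agrees with G1 and with the chosen analysis.

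State two limits alongside it. The contrast removes linear drift only. Carry-over of Seattle-PAP into period 3 would pull the estimate toward zero, which the last-15-minutes window reduces but does not exclude.

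The cost is a change of wording before the results are seen, with no new infants, visits or measurements.
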